## Limitations

4

One key limitation of this study is the relatively small sample size, particularly in the context of post hoc stratification into responders and non‐responders. Given the exploratory nature of the study and the anticipated imbalance in group sizes, the statistical power to detect large between‐group differences is limited. As such, the findings should be interpreted with caution and viewed primarily as preliminary indications of potential QEEG biomarkers associated with treatment response. This limitation constrains the generalizability of the results and precludes definitive hypothesis testing. However, this study serves as a pilot investigation intended to generate effect size estimates and feasibility data that will inform the design and power calculations of future, adequately powered confirmatory studies.

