**Design:**

This multi‐center, assessor‐blinded clinical trial will examine QEEG biomarkers as predictors of rTMS treatment responsiveness in 25 patients with mild cognitive impairment (MCI). Adults aged 60 years or older will undergo cognitive assessments using the Montreal Cognitive Assessment (MoCA) or mini‐mental state examination (MMSE) and have an electroencephalography (EEG) recording. Participants will complete 10 rTMS sessions targeting the left DLPFC over 2 weeks, with 2000 pulses per session at 20 Hz. Cognitive tests will be repeated post‐treatment, and participants will be classified as responders or non‐responders based on cognitive changes, then baseline QEEG parameters will be compared between the two groups. The primary endpoint is the proportion of responders at ten sessions after rTMS (score post‐intervention > score pre‐intervention = responder, according to the minimal clinically important difference (MCID) threshold (i.e., an increase of at least 3 points or 10% on the MMSE, or an increase of at least 1 point on the MoCA); score post‐intervention ≤ score pre‐intervention = non‐responder). The secondary endpoints are the differences in baseline QEEG features between responders and non‐responders.

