Electroencephalography appears to be the preferred paraclinical tool for identifying potential biomarkers of response to magnetic stimulation treatment due to its non‐invasive nature, high temporal resolution, and relative affordability. Furthermore, quantitative EEG (QEEG) further enhances the analysis of EEG data by providing objective and quantitative measures of brain activity, such as power spectral analysis and brain mapping (Fingelkurts and Fingelkurts 2022). This study is conceived as an exploratory investigation aimed at identifying preliminary QEEG biomarkers associated with treatment response to rTMS in individuals with MCI. Designed as a pilot, this study aims to provide foundational insights into the feasibility and potential direction of QEEG analysis in this context, estimating preliminary effect sizes and characterize signal patterns and identifying potential trends, and generating data to inform the design and sample size calculations of future, more definitive trials. By identifying likely responders prior to treatment, the study aspires to optimize resource allocation, reduce the time and costs associated with ineffective interventions, and ultimately improve the quality of care for individuals with MCI.

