#### Secondary Endpoint

1.7.2

Topographic maps will be generated for each QEEG feature (e.g., absolute power, relative power, power ratio, peak frequency, amplitude asymmetry, coherence, and phase lag) for both responder and non‐responder groups using Neuro Guide software, then calculate the average QEEG features for each group using Neuro Guide. Subsequently, the statistical significance of the dissimilarity between the two groups' EEG topographic maps will be determined using independent *t*‐tests or the Mann–Whitney *U* test, depending on the normality of the variables. ROC analysis estimating Area Under the Curve (AUC), sensitivity (SN), specificity (SP), positive predictive value (PPV), negative predictive value (NPV), A positive likelihood ratio (LR+), and the negative likelihood ratio (LR‐) for optimal cut‐points, as well as comparing AUC across biomarkers, will be performed using Stata 18 software. These diagnostic accuracy measures specifically assess the predictive ability of QEEG biomarkers in distinguishing responder from non‐responder status.

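### The pilot is to supply effect sizes for later power calculations, but its QEEG analysis sorts features by significance and AUC, and nothing guards against planning on a selected, upward-biased estimate

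*Protocol article*

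**What the plan says.** The protocol article states the purpose twice. The introduction's last paragraph lists, among the pilot's aims, "generating data to inform the design and sample size calculations of future, more definitive trials". Section 4 (Limitations) calls the study "intended to generate effect size estimates and feasibility data that will inform the design and power calculations of future" confirmatory studies. The same section says that the small sample "precludes definitive hypothesis testing" and refers to "the anticipated imbalance in group sizes".

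The Abstract gives the sample as "25 patients with mild cognitive impairment (MCI"), in one treated group. The Aims and the Conclusion speak of identifying a QEEG biomarker, in the singular.

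Section 1.7.2 is the only QEEG analysis described. It produces maps and group averages for each feature and then determines "the statistical significance of the dissimilarity between the two groups" by t-test or Mann–Whitney test. ROC analysis follows, with accuracy measures at optimal cut-points, "as well as comparing AUC across biomarkers". It mentions no standardised difference or interval, and no rule for which feature's estimate would inform a later sample size.

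**The concern.** The stated product and the stated analysis do not match. A pilot meant to supply effect sizes should be built around estimation, but Section 1.7.2 is built around sorting features by p-value and by AUC.

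Sorting matters because the feature pool is large and the groups are small. Section 1.2.2 lists seven feature types, five bands and 19 channels. Absolute power alone gives 19 × 5 = 95 values. In a sample of 25, a feature stands out partly because chance pushed its observed difference up, so its estimate is biased upward. If that estimate sets the size of the next trial, that trial will be too small and will probably miss a marker that is real.

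Section 4 warns of low power and advises caution. It does not say that low power combined with selection inflates the estimates. Its closing sentence instead offers those estimates as what the pilot contributes.

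**Working it through.** The article gives no sample-size calculation, so there is no stated figure to reproduce. The check asks how large the bias would be if a selected estimate were used.

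**Inputs from the article:** 25 patients in total (Abstract); unequal groups expected (Section 4); features compared by t-test or Mann–Whitney test (Section 1.7.2).

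**Assumptions, because the article does not state them:** two-sided 5% level, no multiplicity correction; a split of 12 v 13, the most favourable, with 8 v 17 and 5 v 20 as the range; true standardised difference d of 0.3, 0.5 or 0.8; next trial 1:1, 80% power, two-sided 5% t-test.

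**Step 1. Smallest observed difference that can be significant.** With 12 + 13 − 2 = 23 degrees of freedom:

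|d| critical = t(0.975; 23) × √(1/12 + 1/13) = 2.069 × 0.400 = 0.83.

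At 8 v 17 it is 0.89, and at 5 v 20 it is 1.03.

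**Step 2. Mean |d| among significant results.** Two-sample t-tests were simulated (at least 200,000 runs per setting). Inflation is mean significant |d| divided by true d.

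**Step 3. Consequence for the next trial.** The per-group size was found once from the true d and once from the mean significant |d|. Power at the true d was then computed for the smaller size.

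| True d (12 v 13) | Chance of p<0.05 | Mean significant \|d\| | Inflation | Needed / planned per group | Shortfall | Real power of next trial |
|---|---|---|---|---|---|---|
| 0.3 | 11% | 1.05 | 3.5-fold | 176 / 16 | 11.0 times | 13% |
| 0.5 | 22% | 1.10 | 2.2-fold | 64 / 15 | 4.3 times | 26% |
| 0.8 | 48% | 1.19 | 1.5-fold | 26 / 13 | 2.0 times | 50% |

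**Step 4. Other splits.** At 8 v 17 the inflation is 3.7-fold (d = 0.3) and 2.3-fold (d = 0.5). At 5 v 20 it is 4.3-fold and 2.7-fold, with shortfalls of 176/11 = 16 times and 64/10 = 6.4 times. Imbalance makes matters worse.

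**Step 5. No selection.** Averaged over all simulated results, significant or not, the estimate is 0.31 at d = 0.3 and 0.52 at d = 0.5, a bias of about 3%. Nearly all the inflation therefore comes from selection.

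**Step 6. Selection by rank instead of p-value.** As a stand-in for choosing the best AUC, take the largest |d| among 20 features at 12 v 13. It averages about 1.1 if every true d is 0.3, and 0.93 if every true d is zero. The 20 features are treated as independent. Real QEEG features are correlated, so this is only an illustration, but it shows that the bias does not need a p<0.05 filter.

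**Step 7. Precision without selection.** For one feature named in advance with d = 0.5, the 95% half-width is 1.96 × √(1/12 + 1/13 + 0.5²/50) = 0.80. Even an unselected point estimate is a weak basis for planning.

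**The case against.** The strongest objection is that the plan states no such rule. A reader might infer from Section 1.7.2 that only significant features are carried into later power calculations. The article does not support that reading: neither purpose statement restricts the effect sizes to significant features, maps and averages are produced for every feature, and ROC analysis is not limited to features that pass a test. AUC is itself an effect size, and comparing several AUCs implies that several are reported. This objection stands, and the inflation figures are therefore conditional. What remains is that the aim is to single out a biomarker, that both sorting tools in Section 1.7.2 inflate whatever they select, and that no sentence guards against using the result.

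A second objection is that Section 4 already urges caution. It does so for power and generalisability, but not for upward bias in the very estimates it offers for planning. That gap is narrow but real.

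A third is that planners of a later trial choose their own target effect, and the article says only that the data will inform them. This is fair, and it limits the severity. The article still presents these estimates as the pilot's product, so it is the natural place for the warning.

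A reader might also object that the promised feasibility data have no endpoint in Section 1.6. An article may leave that to the full protocol, so it is not part of this point. Nor is the mere absence of an effect-size formula.

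**Conclusion.** The concern holds in conditional form. The article makes effect sizes for later power calculations a product of the pilot and says definitive testing is precluded, yet its QEEG analysis is led by significance and AUC comparison. If a feature selected at p<0.05 supplied the planning figure, its estimate would be inflated about 3.5-fold at a true d of 0.3 and 2.2-fold at 0.5, leaving the next trial about 11 and 4 times too small. At 0.8 the problem shrinks to about 1.5-fold and 2 times.

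These sizes rest on an assumed two-sided 5% level, an assumed 12 v 13 split and assumed true effects. The split is the favourable end, since the article expects imbalance. It would go too far to say that the plan will hand on a wrong planning figure; the document neither requires that nor prevents it. This is an inexpensive improvement to a pilot, not a flaw that invalidates it.

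**What to change.** In Section 1.7.2, make estimation the QEEG analysis. Fix the set of features before responders are classified. For every feature in the set, significant or not, report a standardised difference (Hedges g, on the log scale for power features) or an AUC, with a 95% interval. Treat p-values as descriptive.

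In the introduction's purpose statement and in Section 4, add that estimates for features selected in these 25 patients are biased upward and that their point estimates alone should not size a later trial. Name the alternatives: the smallest effect worth detecting, or the confidence limit nearer to no effect for a feature named in advance.

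The cost is a few sentences and a little more analysis, with no extra patients or visits. The drawback is a less favourable planning figure for the next trial.

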## Ethics Statement

Under the identification IR.MAZUMS.REC.1402.18234, the ethics committee of Mazandaran University of Medical Sciences has accepted our study, which is being carried out in compliance with the Declaration of Helsinki. Besides, this study has been registered at the Iranian Registry of Clinical Trials with IRCT registration number IRCT20240218061042N1 (version updated September 7, 2024).

## Consent

All participants will either provide written informed consent to participate in the study or provide assent to have a substitution decision‐maker provide informed consent on their behalf.

## Peer Review

The peer review history for this article is available at https://publons.com/publon/10.1002/brb3.71017

## Data Availability

The datasets generated and analyzed during the current study are available from the corresponding author on reasonable request.
